## Abstract

**Background:**

Increases in life expectancy have resulted in a global rise in dementia prevalence. Dementia is associated with poor wellbeing, low quality of life and increased incidence of mental health difficulties such as low mood or depression. However, currently, there is limited access to evidence-based psychological interventions for people with dementia experiencing low mood and poor wellbeing. Behavioural activation-based self-help, supported by informal carers and guided by mental health professionals, may represent an effective and acceptable solution.

**Methods/design:**

The present study is a phase II (feasibility) single-arm trial informed by the Medical Research Council complex interventions research methods framework. Up to 50 dementia participant/informal carer dyads will be recruited from a variety of settings including primary care, dementia-specific health settings and community outreach. People living with dementia will receive behavioural activation-based self-help and be supported by their informal carer who has received training in the skills required to support the self-help approach. In turn, during the use of the intervention, the informal carer will be guided by mental health professionals to help them work through the materials and problem solve any difficulties. Consistent with the objectives of feasibility studies, outcomes relating to recruitment from different settings, employment of different recruitment methods, attrition, data collection procedures, clinical delivery and acceptability of the intervention will be examined. Clinical outcomes for people with dementia (symptoms of depression and quality of life) and informal carers (symptoms of depression and anxiety, carer burden and quality of life) will be measured pre-treatment and at 3 months post-treatment allocation.

**Discussion:**

This study will examine the feasibility and acceptability of a novel behavioural activation-based self-help intervention designed to promote wellbeing and improve low mood in people living with dementia, alongside methodological and procedural uncertainties associated with research-related procedures. As determined by pre-specified progression criteria, if research procedures and the new intervention demonstrate feasibility and acceptability, results will then be used to inform the design of a pilot randomised controlled trial (RCT) to specifically examine remaining methodological uncertainties associated with recruitment into a randomised controlled design.

**Trial registration:**

Current Controlled Trials ISRCTN42017211

## Background

Dementia is a global healthcare concern, with 115.4 million people worldwide expected to be living with dementia by 2050 [1]. Given there are no current cure or preventative medical interventions [2], dementia represents a significant challenge for health policy [3]. Current estimates indicate that on a global scale, prevalence stands at 35.6 million with 670,000 living with dementia in the United Kingdom (UK) [4]. The provision of long-term support to help people with dementia ‘live well’ is, therefore, a global health and social care priority [5–7].

Developing approaches to facilitate long-term support is especially important given quality of life, increased levels of mortality, increased health and social care costs [8] and poorer functional outcomes [9] commonly experienced by people with dementia [10]. Furthermore, between 30 % [11, 12] and 50 % [13] of people with dementia also experience elevated symptoms of depression. However, despite depression being one of the most common mental health difficulties experienced by people living with dementia [14], access to evidence-based psychological therapies remains limited [15]. This treatment gap [16] exists despite growing evidence identifying cognitive behavioural therapy (CBT) as an effective intervention for treating depression in people with dementia [12], partly due to costs of delivery and a lack of trained therapists [17–19].

To provide a potential solution to address this treatment gap, CBT provided in a self-help format is being introduced into mental health services on a global scale [20–23]. CBT self-help is defined as CBT-specific therapeutic techniques being communicated in the form of bibliotherapy, online, audio or smartphone applications [24, 25] as opposed to delivery by a therapist [24, 26]. Some evidence suggests effectiveness increases when some form of face-to-face, telephone, or email guidance or support is also provided [26–28]. Within the Improving Access to Psychological Therapies (IAPT) Programme implemented across England [29], support is provided by a practitioner-based workforce (Psychological Wellbeing Practitioners (PWPs)) and introduced alongside face-to-face ‘high-intensity’ evidence-based psychological therapies within a stepped care model of delivery [30]. Recent evidence also suggests support can be provided by non-professionals [31]. As such, a potential solution to increase access to psychological therapies for people with dementia may be for non-professionals, such as informal carers defined as those providing unpaid and untrained support within the community to a care recipient [32], to support therapy delivery. The provision of informal carer itself is associated with increased mental health difficulties such as anxiety and depression [33], restriction of social and recreational activities [34] and poor quality of life [35]. Conversely however, other evidence suggests that involving informal carers in the facilitation of psychological interventions for people living with dementia may also improve caregiver mood [36].

Behavioural activation (BA) is a psychological intervention featuring prominently within the IAPT programme [37] and is an evidence-based and cost-effective [38, 39] treatment for depression. BA aims to overcome depression through a structured and graded approach to reintroduce activity into people’s lives to target behavioural avoidance [37] which is common in depression. Specifically, techniques used in BA help reintroduce people to sources of positive-reinforcement within their environment, whilst overcoming sources of negative reinforcement that maintain avoidance behaviours [40]. Several characteristics of the BA self-help protocol utilised within the IAPT programme [40] suggest it may also have potential utility for people with dementia. Not only is BA considered a straightforward approach making it easier for users with dementia and their carers to understand [41] but it may also complement the range of self-management techniques people with dementia and carer dyads already utilise [42]. Initial evidence has already highlighted the potential utility of BA as an effective intervention for treatment of depression in people with Alzheimer’s disease, supported by a therapist and informal carer [36, 43]. However, these studies focused on the use of experienced geriatricians to deliver face-to-face therapy [36, 43], analogous to CBT ‘high-intensity’ support within a stepped care model of delivery [30]. Implementing this ‘high-intensity’ intervention delivered face-to-face by an experienced geriatrician workforce, who may already face immense demands on their time with other aspects of their role may, therefore, be prohibitive and unable to meet the potential demand for treatment [44].

A research programme informed by the Medical Research Council (MRC) complex interventions framework [45] has been undertaken to develop a written BA-based self-help intervention to target low mood and improve wellbeing in people with dementia, supported by their informal carers who themselves are guided in delivering the intervention by a practitioner-based PWP workforce. The current feasibility study builds upon MRC phase I development work [45] previously completed. Recognising the importance of involving people living with dementia and their carers actively in research [46], the phase I study involved semi-structured interviews with people with dementia to develop a new written BA-based self-help intervention to meet the needs of people with dementia. Additionally, two focus groups took place with carers about their role in supporting the person living with dementia work through the materials and problem solve any difficulties encountered under PWP guidance. This protocol represents MRC phase II (feasibility) research [45] to examine methodological, procedural and clinical uncertainties [47, 48]. Should progression criteria for this feasibility study be met, results will inform the design and funding application for a further phase II (pilot) randomised controlled trial (RCT) that will examine methodological and procedural uncertainties specifically related to an RCT design. Subsequent progression of this research programme to a possible future definitive (phase III) RCT will be informed by results from the piloting phase.

### Study aims and objectives

A single-arm feasibility phase II study [45] with an embedded qualitative component examining a number of feasibility questions pertaining to methodological, procedural and clinical uncertainties [47, 48] will be conducted.

The following outcomes will be examined following guidance concerning feasibility study objectives, as distinguished from objectives for a pilot RCT [47]:The intensity of the recruitment procedure in terms of number of invitation packages sent by health professionalsNumber of health professionals required to recruit into the studyThe time taken (up to 6 months) to recruit the a priori determined sample sizeWillingness of clinicians to recruit participants across multiple recruitment settings utilising different recruitment strategiesParticipant response rates between different recruitment techniquesEligibility proportionsParticipant level barriers to recruitment.Study resources required to implement study proceduresFeasibility and acceptability of data collection procedures to participants Feasibility and acceptability of the intervention to participants and clinicians Barriers to clinical delivery Clinician training needs Clinician adherence to the intervention protocol

As determined by pre-specified progression criteria, outcomes will be used to inform the design of a subsequent pilot RCT.

## Methods/design

### Study design

A feasibility phase II single-arm trial [45] with an embedded qualitative sub-study will be conducted. This protocol (version 1, 18/08/2015) is registered on Current Controlled Trials ISRCTN42017211 and follows Standard Protocol Items, Recommendations for Interventional Trial (SPIRIT) [49] guidelines for reporting interventional trials.

### Setting

Four different settings—general practitioners (GPs), specialist dementia healthcare settings employing Primary Care Dementia Practitioners (PCDP), memory clinics and community outreach in the county of Cornwall (southwest England)—will be utilised to examine feasibility outcomes associated with recruitment. All treatment will be provided by PWPs within ‘step 2’ of an IAPT primary care mental health service adopting a stepped care model [30]. Recruitment setting locations have been selected on the basis of locality of study PWPs from the IAPT service to help increase the feasibility of intervention delivery. Further, recruitment setting types were selected on the basis of recruitment strategies utilised in other depression [50–52] and dementia studies [53, 54].

### Eligibility criteria

#### People living with dementia

Participants are included if they:Have a diagnosis of probable dementia recorded in medical records, with no restriction placed on dementia type given evidence suggesting mixed dementia is the most common dementia presentation [55]Have mild-to-moderate dementia severity defined as scoring between 12 and 24 on the mini-mental state examination (MMSE) [56]Have a score of 4 or more on the 12-item Geriatric Depression Scale (GDS-12R) [57]Residing at homeAble to provide informed consent or have an informal carer willing to provide consultee consentHave sufficient proficiency in English to read and engage with the BA-based self-help materialHave an informal carer (defined as a partner, family member or friend) who has regular contact (at least weekly) with the person with dementia and willing to support the intervention.

Participants receiving antidepressant medication and/or acetyl-cholinesterase inhibitors or memantine will also be able to participate if they have been receiving a stable dose for at least 1 month before recruitment. No upper or lower age restrictions are placed on people living with dementia.

Participants are excluded if they:Have a co-morbid diagnosis of a severe and enduring mental health problem including psychosis, type I or II bipolar disorder and personality disorder recorded in medical records or self-reported to the study teamAre currently receiving formal psychotherapy or another potentially active psychological treatmentAre acutely suicidal and/or have a history of persistent self-injuryHave self-report or medical record documented misuse of alcohol, prescription drugs or street drugs, so severe it interferes with the person with dementia’s ability to perform normal activities in daily life and engagement with the intervention

Exclusions 1–3 are informed by guidance indicating that CBT self-help is not suitable for the specific population identified or that people with depression should only receive one psychological intervention at a time [58].

#### Informal carers

Participants are included if they are:Aged 16 years or over.Self-identified informal carer of a person with dementia with regular contact (at least weekly) with the person with dementiaWilling to support the intervention, including increasing contact to facilitate supporting the intervention if required

Participants are excluded if they:Score over 20 on the Patient Health Questionnaire-9 (PHQ-9) indicating severe levels of depression [59]Have a co-morbid diagnosis of a severe and enduring mental health problem including post-traumatic stress disorder (PTSD), psychosis, type I and II bipolar disorder or personality disorder as recorded in medical records or self-reported to the study teamHave self-report or medical record documented misuse of alcohol, prescription drugs or street drugs, so severe it interferes with the informal carer’s ability to perform normal activities in daily life and engagement with the interventionHave difficulties reading or following the written BA self-help materialAre acutely suicidal and/or have a history of persistent self-injury

The exclusion criteria for informal carers are based upon clinical factors that may impair and interfere with an informal carer’s ability to support and engage in the intervention and indicate the carer themselves may require psychological support.

To be included within the study, both members of the dyad (person with dementia and informal carer) need to meet the inclusion criteria. In the case of a person with dementia being eligible for inclusion, but an informal carer ineligible, the researcher will work with the dyad to identify if another informal carer known to the dyad may be willing to participate in the study.

### Recruitment settings and procedure

A multifaceted recruitment approach will be employed, building on techniques used to successfully recruit carers of people with dementia [54] across four specific recruitment settings (see Fig. 1).

**Fig. 1 Fig1:**
[figure not shown]
Flow of participants through the study

#### GP records

GP search and mail-out will be adopted as used successfully in a number of depression trials [50–52]. GP electronic case records will be searched for people with a formal diagnosis of dementia, and a manual screen will be performed to check against the inclusion criteria. Reasons for exclusion will be anonymised and provided to the research team [60]. Participant invitation packages (study invitation letter, study summary sheet, reply slip and reasons for refusal of participation questionnaire) will be sent to people with dementia included in the screen. This package will also include a separate study invitation package to be passed onto an informal carer. People with dementia, or informal carers, will be able to contact the research team by returning the reply slip, telephoning or emailing the research team. Given that telephone reminders by clinicians have been reported to increase recruitment rates [61], non-responders will be provided with telephone follow-up calls by general practice staff. Where phone calls receive no answer, a maximum of four attempts to establish contact will be made over this time period. GPs can also directly refer suitable people with dementia. Study posters and brochures will also be displayed in practice receptions to further advertise the study.

#### Primary care dementia practitioners

PCDPs will perform a search and mail-out. Drawn from a variety of backgrounds in health care, PCDPs are health professionals specialising in dementia care providing support to people living with dementia and their families in the community. PCDPs will screen caseloads to check against the inclusion criteria. Reasons for exclusion will be anonymised and provided to the research team. Study invitation packages will be sent in a manner consistent with that used for GP record recruitment or handed to potential participants face-to-face. It is anticipated that PCDPs will complete their initial search and mail-out within 1 month of the study commencing recruitment with any patients added to their caseload over the 6-month recruitment period being invited face-to-face. PCDPs will provide non-responders with telephone reminders (maximum of four attempts) and can also directly refer suitable people with dementia during the course of the study.

#### Memory service

The memory service (Consultant in Old Age Psychiatry and Memory Assessment Nurses) will recruit potential participants using two methods: (1) post-diagnostic assessments with memory service staff administering the PHQ-2, a two-item screen for possible depression [62, 63], with people with dementia screening positive for possible depression provided with a study invitation package and (2) a search and screening of the memory service database for people who have received a diagnosis of dementia over the preceding 24 months with those identified as potentially eligible being sent the study invitation package in the post. In the case of post-diagnostic assessments only, the administration of the PHQ-2 screen is included within the recruitment procedure to help minimise the number of people invited into the study who do not experience low mood or depression. Post-diagnostic assessments are conducted by health professionals experienced in screening for depression (Consultant in Old Age Psychiatry and Memory Assessment Nurses) and are the only consistent face-to-face recruitment strategy utilised in the study. As such, administration of the PHQ-2 screen will only take place in this recruitment centre. Other face-to-face recruitment techniques (e.g., GP or PCDP referral) are designed to be more opportunistic and time limited, as such the addition of a PHQ-2 screen was not deemed necessary. Given that depression status may have changed since post-diagnostic assessment, people with a diagnosis of dementia recorded on the memory service database will be invited to participate in the study whether or not they have a record of depression documented. Memory service staff will provide non-responders with telephone reminders (maximum of four attempts). Anonymised reasons for exclusion from both the post-diagnostic assessments and database screen will be provided to the research team.

#### Community outreach

A number of community-based organisations including Memory Cafés, Memory Matters South West, the Alzheimer’s Society, Carers Forum, Disability Cornwall, Dementia Action Alliance, Age UK, Cornwall Carers and Penwith Community Development Trust will be approached to support the study by distributing flyers and invitation packages and displaying posters. In addition, the study will be advertised by distributing study posters and leaflets in other community locations including community day care centres; libraries, banks, bus stops, post offices, supermarkets, cafes and community centres.

#### Reasons for refusal of participation

Across all recruitment settings, study invitation packages will include refusal of participation forms for both the person with dementia and informal carer for those who do not wish to participate. The form includes a questionnaire listing possible reasons for refusal of participation informed by previous research [64] as well as an open-ended question to provide further reasons if wished. Each package also includes a freepost envelope to enable people with dementia and their carers to return refusal of participation forms to the study team. These data will be used to inform barriers of recruitment and the acceptability of the proposed intervention.

### Sample size

A primary aim of this study is to examine the recruitment of participants, through a variety of techniques; therefore, the study will not stipulate a sample size a priori. Instead, to facilitate comparisons between the effectiveness of the recruitment approaches adopted, the study will continue to recruit until a maximum cut-off of 50 dyads (100 participants). Fifty dyads will enable the estimation of a follow-up rate of 80 % with a margin of error of 14 % based on the lower bound of the 95 % confidence interval.

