### Feasibility outcome measurements (primary outcome measurements)

Data related to study feasibility will be collected to examine the primary study objectives relating to methodological, procedural and clinical uncertainties [47, 48]. Following guidance concerning feasibility study objectives [47], Table 2 provides a summary of feasibility outcomes to be examined, alongside progression criteria (where applicable) to be met in order to progress to develop an application for phase II pilot RCT funding [45].

**Table 2 Tab2:** Feasibility data and method of measurement

Feasibility outcome	Measurement	Progression criteria to phase II pilot RCT
Recruitment	Quantitative data	
	Percentage of people with dementia invited into the study/number of people with dementia in total identified by health professionals	No criteria set
	Number of health professionals required to assist with recruitment into the study	No criteria set
	The time taken (up to 6 months) to recruit up to 50 dyads	No criteria set
	Number of dyads enrolled into the study per week	2 dyads per week
	Percentage of dyads willing to undergo screening/number invited (calculated for GP, PCPD and memory service recruitment)	≥15 %
	Percentage of dyads overall meeting the inclusion criteria/number invited	≥5 %
	Percentage of dyads overall enrolled in the study/number invited	≥5 %
	Qualitative data	
	Reasons for exclusion reported to the research team during health professional screening (GP, PCPDs, memory service)	No criteria set
	Reasons for ineligibility	No criteria set
	Identified barriers to recruitment (reasons for refusal of participation)	No criteria set
Attrition	Quantitative data	
	Percentage of dyads completing post-treatment (3 month) outcome measures	≥70 %
	Reasons for dropout	No criteria set
	Qualitative data	
	Acceptability interviews with non-attendees and poor attendees (informal carers and people with dementia)	No criteria set
Data collection procedures	Quantitative data	
	Time taken and number of sessions to administer the screening measures	≤2 h; ≤2 sessions
	Time taken and number of sessions to administer the baseline assessment	≤2 h; ≤2 sessions
	Time taken and number of sessions to administer the follow-up assessments	≤2 h; ≤2 sessions
	Percentage of missing items per questionnaire	≤10 %
	Qualitative data	
	Acceptability interviews with participants concerning acceptability of research procedures	No criteria set

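### Three progression percentages divide by everyone invited, so invitations still open when recruitment closes count as failures, which penalises the routes that invite throughout the period

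*Protocol article*

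**What the plan says.** The Sample size section sets one ceiling for all four recruitment settings and gives its purpose: "to facilitate comparisons between the effectiveness of the recruitment approaches adopted, the study will continue to recruit until a maximum cut-off of 50 dyads". There is no quota or minimum open period per setting. The only precision statement there concerns retention: "Fifty dyads will enable the estimation of a follow-up rate of 80 % with a margin of error of 14" %, taken at the lower confidence limit.

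Table 2 bounds the recruitment period ("The time taken (up to 6 months) to recruit up to 50 dyads") and sets a pace criterion of 2 for "Number of dyads enrolled into the study per week". It then sets three criteria per person invited: at least 15 % of dyads willing to be screened (GP, dementia-practitioner and memory-service settings), at least 5 % for "Percentage of dyads overall meeting the inclusion criteria/number invited", and at least 5 % enrolled.

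Invitations go out on different calendars:
- **Primary care dementia practitioners (PCDPs).** It is anticipated that "PCDPs will complete their initial search and mail-out within 1 month of the study commencing recruitment". Patients who join the caseload later are invited in person over the 6 months.
- **Memory service.** One stream is a mail-out to people diagnosed in the preceding 24 months. The other invites people at post-diagnostic assessments.
- **GP records.** This is a search and mail-out with no stated timing.

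Between invitation and enrolment come a reply, up to four reminder calls to non-responders, a consent visit, a screening assessment and a separately arranged baseline (recruitment sections; Informed consent, screening and baseline).

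**The concern.** A percentage per person invited measures willingness or eligibility only if each invitation has had time to run its course. Here recruitment ends on one date for everyone, at the 50th dyad or at 6 months, and the denominator is simply the number invited. Someone invited shortly before that date is in the denominator with almost no chance of reaching the numerator.

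Two things are at stake. The three percentages are conditions for progressing to the pilot trial, and they are pulled downward. The planned reporting by setting would also show a lower yield for a route that invites up to the end than for one that mailed out early, even if the two were equally good. That works against the comparison of approaches that the Sample size section gives as the reason for recruiting up to the cap.

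**Working it through.** **The plan's own figure.** The exact 95 % interval for 40/50 is 66.3 % to 90.0 %. The lower-side margin is 80 − 66.3 = 13.7 points, which rounds to the stated 14 %. The figure is right, but it describes follow-up and says nothing about the precision of a comparison between recruitment routes.

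**When the cap binds.** Inputs: 50 dyads, and 6 months taken as 26 weeks. Weeks to cap = 50 / rate; share of the window lost = 1 − weeks/26.

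| Dyads per week | Weeks to cap | Window lost |
|---|---|---|
| 1.5 | 33.3 (not reached) | 0 |
| 2 (Table 2 criterion) | 25 | 4 % |
| 3 | 16.7 | 36 % |
| 4 | 12.5 | 52 % |

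The cap binds only above 50/26 = 1.92 dyads per week.

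**When the cap alone fails the 5 % enrolment row.** The ceiling of enrolled/invited is 50 / invitations: 10 % at 500, 5.0 % at 1000, 4.0 % at 1250 and 3.3 % at 1500. Failure from the cap alone therefore needs more than 50/0.05 = 1000 invitations. As an illustration, with 1250 invitations and a true yield of 8 % (100 dyads), the observed value would be 50/1250 = 4 %. The article gives no invitation total.

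**The 6-month close without the cap.** Assume a route invites evenly over 26 weeks and the mean time from invitation to enrolment is L weeks. About L/26 of its eventual enrolments then fall after closure, so the observed yield is about the true yield × (1 − L/26). With a true yield of 8 %:
- L = 4: 8 × (1 − 4/26) = 6.8 %
- L = 6: 8 × (1 − 6/26) = 6.2 %
- L = 8: 8 × (1 − 8/26) = 5.5 %

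A route that mailed everything in month 1 would read close to 8 %.

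**Both together.** An illustrative simulation used two routes, each with a true yield of 8 % and a mean lag of 6 weeks. The early route sent all invitations in the first 4 weeks; the continuous route spread them over 26 weeks. Recruitment closed at 50 dyads or week 26.

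| Invitations early / continuous | Runs in which the cap binds | Observed yield, early | Observed yield, continuous |
|---|---|---|---|
| 300 / 300 | 14 % | 8.0 % | 6.1 % |
| 500 / 300 | 89 % (mean closing week 18) | 7.7 % | 5.3 % |

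In the first row nearly all of the gap comes from the 6-month close. In the second the cap adds to it. Volumes, yield and lag are assumptions. The direction follows from the invitation calendars in the article.

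**The case against.** The strongest reply is that the article never says unresolved invitations stay in the denominator. It also does not say that mail-outs are sent in one block or continue near the cap, and only the PCDP mail-out has a stated timing. That is true. The retained denominator is the plain reading of the wording in Table 2, not a declared rule. It matters because no other rule is given for criteria that decide progression.

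A reader might infer that the cap defeats the comparison outright, or that quick recruitment will make the progression decision fail. The documents do not support either. At the protocol's own pace of 2 per week the cap costs about one week. A false failure of the enrolment row from the cap alone needs more than 1000 invitations, and nothing shows that so many are planned. Data are collected by setting, where possible, until closure, so the comparison is shortened and tilted, not lost. No progression criterion compares settings.

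It is also tempting to say that all the criteria are affected. Follow-up, missing items and adherence are not, and the weekly enrolment rate is not if it is divided by the weeks actually open. The 15 % row counts willingness, which can still be recorded after the last place is filled, so it is depressed only if later replies go uncounted.

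Finally, a fixed recruitment period always cuts off late invitations. That is so, and it is a reason to define the denominator accordingly.

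**Conclusion.** The point holds in a limited form. Taken as written, the three per-invitation percentages are biased downward by invitations unresolved at closure, and the bias falls hardest on the routes that invite throughout the period.

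The cap's contribution is minor at about 2 dyads per week and becomes material at 3 or more. The contribution of the 6-month close does not depend on pace. Under assumed mean lags of 4 to 8 weeks it takes roughly 15 % to 31 % (4/26 to 8/26) off the apparent yield of a continuously inviting route. A true overall yield of 6 % would read below 5 % once more than one-sixth of eventual enrolments are cut off (6 × 5/6 = 5).

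These sizes rest on the assumed lag and on even invitation over 26 weeks. Whether a progression decision would actually change cannot be determined, because neither the number of invitations nor their timing outside the PCDP mail-out is given.

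**What to change.** 1. Keep a dated invitation log for each setting.
2. In Table 2, calculate the three percentages, overall and by setting, on invitations issued at least a fixed response window before recruitment closed. Take numerator and denominator from the same invitations. Set the window in advance, long enough for reply, reminder calls, consent, screening and baseline.
3. After the cap is reached, keep logging dyads who reply as willing, under a label such as 'willing, cap reached', and count them in the 15 % row.
4. Report weeks open for each setting beside its yield.

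**Cost.** The change needs a log, revised wording in Table 2 and no extra participants. The latest invitations leave the denominator, so precision falls slightly. With an assumed 6-week window and closure at week 26, a route sending 300 invitations evenly would lose 300 × 6/26 = 69. Its interval would be about √(300/231) = 1.14 times as wide. With 500 early invitations added, the overall factor is √(800/731) = 1.05. The loss is larger if the cap is reached within a few weeks of a large mail-out.

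Sending mail-outs in batches would reduce that loss, but it is optional. At 2 dyads per week there is only about one week of slack before the 6-month limit.
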